### Interventions

#### Smoking Cessation and Relapse Prevention Interventions

The presentation of the smoking cessation intervention content has been based mainly on the taxonomy of behavior change techniques in interventions [7] and the taxonomy of behavior change techniques used as support for smoking cessation [39]. The theoretical frameworks that the techniques are based on are control theory [40], the social-cognitive theory [41], the theory of planned behavior [42], and the motivational interviewing technique [43]. During the first session, baseline data are collected and then a group or individual motivational interview session takes place for about an hour, aiming to motivate participants to take further responsibility for making important health-related behavior changes (ie, to gradually decrease smoking and be more physically active). During the second session, participants discuss the barriers for behavior change and they brainstorm facilitators to apply. In the third session they set specific goals and make plans for behavior change. In this meeting, participants also set a quit day and they get training on the use of pedometers. The 3 sessions are scheduled weekly. The intervention is a shorter version of a previously effective intervention named “No more smoking! It’s time for physical activity” [44-45]. Multimedia Appendix 2 contains a more detailed overview of the contents of the intervention used to help participants quit smoking.

All sessions are delivered by the study nurse, who has previous experience with counseling smokers to quit. Multimedia Appendix 3 presents the content of the fourth session that covers relapse prevention, which is held for the participants within 1 week after their quit day. The aim of this fourth session is to help participants develop a cravings management plan to prevent relapses. Similarly, the presentation of the fourth session’s content has been based on the taxonomy of behavior change techniques used as support for smoking cessation [39] and in general interventions [7]. The theoretical frameworks that the techniques are grounded in are the relapse prevention model [46,47], control theory [40], social-cognitive theory [41], and the theory of planned behavior [42].

#### Database and Data Collection Mechanism of the Ph.o.S App

The mHealth mobile phone application, Ph.o.S, and its data collection mechanism was developed by a software designer affiliated with the University of Jyvaskyla, as a project researcher at Agora Center. Additional support for the development was provided for graphic design and user interface design by 2 students from the IT department. Table 2 presents examples of the database contents by category (eg, introductory messages, physical activities, and motivational messages). The database contents are based on the relapse prevention model [46,47] and the behavior change techniques for smoking cessation via text-messaging intervention [10]. Additionally, the Ph.o.S app was designed according to the principles of persuasive systems design [48]. For example, the principles of tailoring [49], personalization, suggestion, praise, trustworthiness, and expertise have been used in the design of the application. The application database includes a pool of 57 introductory messages, 49 motivational messages, and 64 physical activities, all of which are coded to appear according to the users’ profile and status. Introductory and motivational messages were reviewed by 3 experts on health and exercise psychology and physical activities by 2 experts on sport and exercise science. Multimedia Appendix 4 includes examples of screenshots of the sequence from a sample usage session.

During the fourth session, experimental group participants are instructed to use the application whenever they experience cigarette cravings and to give feedback for every use. As a result, data entries are self-initiated whenever participants use the app. The Ph.o.S. app is installed on participants’ personal mobile phones, but if they do not have a mobile phone, then a device is provided by the study team. No incentives are provided to use the app or to complete data during the entire follow-up assessment period. When they need to, participants can use the app without an Internet connection. All information is uploaded to the server as soon as the device is connected. Participants’ identification number and profile settings are entered when the Ph.o.S app is installed on their mobile phones and used for the first time. Profile settings include gender, age, weight, and height, days since quit date, the origin of the decision to quit, and heavy and moderate intensity physical activity history during a typical week (screenshot 1, Multimedia Appendix 4). After that, every time a user experiences a craving situation, specific information regarding mood (eg, positive, neutral, negative), place (eg, home, at work, outdoors), and social environment (eg, alone, not alone) are requested (screenshot 2, Multimedia Appendix 4). According to users’ profile information and the situational status, a variety of animated physical activities, matched with introductory and motivational messages, are suggested. Physical activities were animated to model/demonstrate the suggested activities in a visual form (screenshot 3, see Multimedia Appendix 4). Each time the participant uses the app, he or she is asked to provide feedback on the effectiveness of the app to manage the craving. Answer options are the following: “Yes it worked,” “No, but I’ll manage,” or “No, I relapsed” (screenshot 4, see Multimedia Appendix 4). Multimedia Appendix 5 shows the CONSORT checklist for this study.

**Table 2 table2:** Ph.o.S app: examples of database content.

Category	Examples	Behavior change techniques
Introductory messages	Researchers have found 70 poisonous chemicals in cigarettes which cause cancer. Stay healthy!	Provide information on consequences of behavior in general
	Your shortness of breath when using stairs is much less now!	Provide information on consequences of behavior to the individual
	Ex-smokers have less than two cravings a day. You can manage this craving!	Provide normative information about others’ behavior
	You are a good example to others every day you stay away from smoking!	Prompt identification as role model/position advocate
	Is it worth giving up what you’ve worked so hard for? Definitely not!	Prompt anticipated regret
	Walk proudly! You are doing an amazing job quitting!	Prompt rewards contingent on effort or progress toward behavior
	
Physical activities	Walking: Walk and every 10 steps say: You can make it!	Behavioral substitution + Prompt self-talk
	Brisk walking: Walk briskly and every 15 steps say: You can do this!	Behavioral substitution + Prompt self-talk
	Stairs: Find a stairway to go up and down!	Behavioral substitution
	Breathing: Inhale for a count of 4, then exhale for a count of 4.	Behavioral substitution
	Tension release: Grab a ball and squeeze it with your right hand and then with your left hand.	Behavioral substitution
	Stretching: Stretch your upper arms. Hold for 10 seconds.	Behavioral substitution
	Balance: Balance on your right leg and then on your left leg for 5 seconds.	Behavioral substitution
	Strength: Do as many push-ups as you can in a row.	Behavioral substitution
	Isometric: Hold the superman position for 5 seconds.	Behavioral substitution
	Dance: Listen to your favorite song and dance!	Behavioral substitution
	Gardening, cleaning home physical activities: Do some housework!	Behavioral substitution
	
Motivational messages	Pain is temporary. Quitting is forever!	Facilitate relapse prevention and coping
	I can keep going!	Enhance self-regulation
	Never be a slave to cigarettes again!	Motivation to remain abstinent
	Do not go back! You are a permanent ex-smoker now!/You are a healthy ex-smoker!	Motivation to remain abstinent
	Concentrate on your goal!	Maintain engagement
	It’s not the situation; it’s your reaction to the situation!	Provide information on withdrawal symptoms
	I want to feel like a winner, not miserable after 3 minutes!	Prompt anticipated regret
	My actions are always within my control.	Self-regulation/self-control

### Participant Retention

To prevent missing data, an effort will be made to retain the participants in the trial for the follow-up data collection. However, participants who withdraw their consent will discontinue their participation in the study. Moreover, participants who attend less than 2 out of 3 sessions of the quit smoking intervention will be excluded from the final analysis. Participants who drop out of the trial or who are lost for follow-up are considered to be smoking. The flow of the participants is presented in Figure 1.

The strategies for monitoring and improving adherence to intervention protocols include the following:

Face-to-face adherence reminder. Study participants will be well informed during the first session about the expectations regarding study procedures before they sign the informed consent form. Moreover, a reminder about the expected participation during the follow-up measures takes place during the fourth session when they are asked about their preferred way of follow-up data collection (eg, telephone, mail, email or SMS).Providing feedback about how well subjects adhere to protocol and achieve target goals whenever possible. During the follow-up period a short SMS or email message will be sent to all participants (ie, both experimental and comparator). The follow-up messages start with an acknowledgment of the participant’s contribution to date (ie, how well they adhere to the protocol), followed by a motivational message that is individualized depending on their progress (ie, relapse or no relapse). Next, information on how to fill out the follow-up questionnaire is provided and, finally, the date of the next follow-up point is reported.Monitoring adherence to the Ph.o.S app use and intervening when adherence problems emerge. In the experimental group, adherence is monitored by recording through the data collection mechanism of the Ph.o.S app. When participants do not use the Ph.o.S app for 1 week, they are asked, via SMS or email, to verify if they use the Ph.o.S app, to check if there is a technical problem, or if they have stopped using the Ph.o.S app. If they answer that they do not use the app, then they are sent a link to a short questionnaire in order to assess the reasons for discontinuing use of the app. Participants are considered dropouts when they do not respond to the invitation emails for measurement but not when they stop using the app.

**Figure 1 figure1:**
[figure not shown]
Study flowchart: The diagram illustrates the flow of participants.

## Results

### Primary Efficacy Measure

Point prevalence abstinence (PPA) will be the primary outcome and the primary efficacy parameter for the study. The main outcome analyses are based on 7-day PPA (ie, reported abstinence of at least 7 days prior to each scheduled follow-up). PPA and prolonged abstinence are closely related and can be interconverted with moderate accuracy [50]. Self-reports of smoking behavior over the last 7 days are collected from participants at the fourth session (*t*
_1_), 3 days after the fourth session day (*t*
_2_), weekly after the fourth session day through week 4 (*t*
_3_-*t*
_6_), and at weeks 12 (*t*
_7_) and 24 (*t*
_8_) after the fourth session day. Self-reported PPA at the *t*
_1_ and *t*
_8_ follow-ups are verified by saliva cotinine (with a cutoff value of 10 ng/mL) for stated abstinence using NicAlert saliva-cotinine tests [51]. The timeline follow-back for smoking is used to assess daily smoking intensity [52] in a small 1-week calendar form on paper to record how many cigarettes they smoked each day in the last 7 days.

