### Secondary Efficacy Measures

The secondary efficacy parameters for the study include the following measures:

The self-reported number of relapses, which is assessed through a single item asking participants to complete the number of relapses they had the last 7 days. Data are collected from participants at the fourth session (*t*
_1_), 3 days after *t*
_1_ (*t*
_2_), weekly from *t*
_1_ through week 4 (*t*
_3_-*t*
_6_), and at weeks 12 (*t*
_7_) and 24 (*t*
_8_) after *t*
_1_.The self-reported number of cravings, which is assessed through a single item asking participants to complete the number of cravings they experienced in the last 7 days. Data are collected from participants at the fourth session (*t*
_1_), 3 days after *t*
_1_ (*t*
_2_), weekly from *t*
_1_ through week 4 (*t*
_3_-*t*
_6_), and at weeks 12 (*t*
_7_) and 24 (*t*
_8_) after *t*
_1_.Self-efficacy on being aware of experienced cravings, which is assessed with the single item: “How well are you aware of your cigarette cravings?” Answers are given on a 10-point scale from 1 (very poorly) to 10 (very well). Data are collected from participants before the quit day (-*t*
_2_), at *t*
_1_, *t*
_2_, weekly from quit day at *t*
_3_-*t*
_6_, and at weeks *t*
_7_ and *t*
_8_.Self-efficacy on managing cravings, which is assessed with the single item: “How well do you manage your cravings?” Answers are given on a 10-point scale from 1 (very poorly) to 10 (very well). Data are collected from participants at -*t*
_2_, *t*
_1_, *t*
_2_, weekly at *t*
_3_-*t*
_6_, and at weeks *t*
_7_ and *t*
_8_.Power of control in managing cravings is assessed with 6 items. An example item is “If I am in a situation where I celebrate with my friends...,” then, the answer for the experimental group is “It will be more difficult to use Ph.o.S. app to control my craving for tobacco,” and for the comparator group is “It will be more difficult to do something to control my craving for tobacco.” Answers are given on a 7-point scale from 1 (totally agree) to 7 (totally disagree). The other items present similar tempting situations like when participants are stressed or angry. Data are collected from participants before the quit day at -t_2_ and -t_1_ and after *t*
_1_ at weeks t_2_, t_6_, t_7_, and t_8_.

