### Statistical Methods

Generalized linear mixed models will be used to examine differences between the groups on the dichotomous primary outcome variable: abstinent versus smoker status at the 6-month follow-up time point (ie, *t*
_8_). The differences at all follow-up time points will also be examined, but the 6-month follow-up is considered to be the primary focus. Descriptive statistics will be used to report process data. Any covariates identified in the preliminary analyses will be added to the model. Linear mixed models will be used to analyze the secondary efficacy measures for data that are normally distributed or are approximate to a normal distribution (via data transformations). For count variables, a generalized Poisson mixed model will be applied. Alternatively, we will use nonparametric tests by time point separately.

Finally, 3 separate logistic regressions on the primary dichotomous outcome (abstinent-smoker) will be performed using the theory of planned behavior (TPB) constructs of quit smoking behavior and increased physical activity behavior at the -*t*
_2_ time point and the TPB constructs of manage cravings behavior at the *t*
_1_ time point as predictors. Linear regressions for the continuous variables of the secondary efficacy outcomes will be used to test the predictive ability of all TPB constructs. All analyses will be conducted using intent-to-treat principles with participants remaining in their originally assigned groups after randomization regardless of adherence or protocol deviation. This is done to increase the likelihood that group differences are due to the intervention and unaffected by biases that lead to an overestimation of the intervention effect [56].

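### The 7-day look-back can reach before the quit day at t1 and mostly precedes app training at t2, so the early group comparisons are mislabelled or diluted; t8 is unaffected

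*Protocol article*

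**What the plan says.** All places are in the protocol article.

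- **Outcome definition** (Primary Efficacy Measure): 7-day PPA means "reported abstinence of at least 7 days prior to each scheduled follow-up". No exception is made for any assessment.
- **Assessment times** (same section): "Self-reports of smoking behavior over the last 7 days are collected from participants at the fourth session" (t1), then "3 days after the fourth session day" (t2), then "weekly after the fourth session day through week 4" (t3 to t6), and at weeks 12 and 24 (t7, t8).
- **Timing of the fourth session** (Smoking Cessation and Relapse Prevention Interventions): a session "which is held for the participants within 1 week after their quit day". No exact day is fixed.
- **Start of the app** (Database and Data Collection Mechanism of the Ph.o.S App): "During the fourth session, experimental group participants are instructed to use the application whenever they experience cigarette cravings".
- **Counts** (Secondary Efficacy Measures): relapses come from a single item "asking participants to complete the number of relapses they had the last 7 days". The craving item uses the same window. Both are asked at t1, t2 and t3.
- **Analysis** (Statistical Methods): t8 is the primary focus, but "The differences at all follow-up time points will also be examined". Counts go into a Poisson mixed model or, alternatively, into tests at each time point.
- **Status of t1**: Primary Efficacy Measure groups t1 with t8 as follow-ups at which self-report is checked by cotinine. Table 1 in Trial Design marks t1 as the fourth-session intervention and starts follow-up assessment at t2.

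**The concern.** A 7-day window has its intended meaning only if all 7 days lie after the event that starts the period of interest. For abstinence after quitting, that event is the quit day. For the effect of the app, it is the fourth session, the first point at which the two arms are treated differently.

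At t1 and t2 the window can start before one or both of these events. Two things follow. PPA at t1 can record a successful quitter as a smoker because of cigarettes smoked before the quit day. At t2, the first assessment after app training, most of the reported week belongs to a period in which the arms were treated the same, so a real early difference would look smaller than it is.

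This matters because the main hypothesis in Trial Aim is worded for abstinence over the follow-up measures, and Statistical Methods plans group comparisons at all of them.

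**Working it through.** The plan gives no figure to reproduce here, so the check is calendar arithmetic.

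**Inputs.** Day 0 is the quit day. The fourth session is on day d, with d from 1 to 7 because the article says only that it falls within a week. t2 is day d + 3, t3 is day d + 7 and t4 is day d + 14. A 7-day look-back on day x covers days x - 7 to x - 1. This is my convention, with day 0 taken as the first smoke-free day.

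**Days before the quit day**

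- t1 window: days d - 7 to d - 1, so pre-quit days = 7 - d.
- t2 window: days d - 4 to d + 2, so pre-quit days = max(0, 4 - d).
- t3 window: days d to d + 6, so pre-quit days = 0.

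| d | t1 | t2 | t3 |
|---|---|---|---|
| 1 | 6 | 3 | 0 |
| 2 | 5 | 2 | 0 |
| 3 | 4 | 1 | 0 |
| 4 | 3 | 0 | 0 |
| 5 | 2 | 0 | 0 |
| 6 | 1 | 0 | 0 |
| 7 | 0 | 0 | 0 |

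The t1 window is wholly post-quit only at d = 7, and the t2 window from d = 4 on.

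**Days before app training (any d).** Counted from the session day, the windows are:

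- t1: days -7 to -1, so 7 of 7 precede training.
- t2: days -4 to +2, so 4 of 7 (57%) precede training.
- t3: days 0 to +6, so none precede training.

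**Overlap (any d)**

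- t1 and t2 share days -4 to -1: 4 days.
- t2 and t3 share days 0 to +2: 3 days.
- t1 and t3 share none, and t3 and t4 share none.
- 4 + 3 = 7, so every day of the t2 window is also reported at t1 or t3.

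**Size of the dilution in the t2 counts.** Assume a constant daily rate m without the app, and a rate r x m in the app arm after the session. A window wholly after training would show an expected difference of 7m(1 - r). The t2 window shows 3m(1 - r), which is 3/7 (43%) of it. For PPA there is no such simple factor, but anyone who smoked in the 4 pre-training days is a smoker at t2 whatever the app did afterwards.

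**Time at risk for relapse.** A relapse can occur only after quitting. The days at risk inside the window are therefore d at t1 (1 to 7) and min(7, d + 3) at t2 (4, 5, 6, then 7), so they differ between participants with an early and a late fourth session.

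**The case against.** The strongest reply is that little depends on t1 and t2. The primary comparison and the power section concern 24 weeks, and no window from t3 on reaches before the quit day or the app. That stands, and it limits the point to the early secondary comparisons.

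A second reply is that t1 precedes the app by design and can serve as a baseline. That stands too. The difficulty is that the article treats t1 as a follow-up in one place and not in another, and a baseline that counts pre-quit smoking still does not measure abstinence since quitting.

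Four stronger readings are tempting, and the documents do not support them:

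- **Bias towards one arm.** Pre-quit days enter the windows of both randomised arms alike. The harm is mislabelling and dilution.
- **Events counted twice in a total.** The t1 to t3 windows add up to 21 reported days but cover 14. No section sums counts over assessments, however. The planned analyses are a mixed model, which does not require independent observations within a person, or separate tests. The overlap means only that adjacent observations share days.
- **A fixed share of quitters misclassified.** If d were uniform over 1 to 7, 6 of 7 (86%) would have pre-quit days at t1 and 3 of 7 (43%) at t2. The article gives no distribution for d, and sessions clustered near day 7 would shrink both figures. Misclassification also requires smoking on those days. The sessions encourage gradual reduction, and people already trying to quit are admitted.
- **Pre-quit cigarettes inflating relapse counts.** A relapse presupposes quitting, so participants would not naturally report them as relapses. For that item the issue is unequal time at risk.

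**Conclusion.** The point holds for t1 and t2 only. At t1, a participant who smoked up to the quit day and stopped completely is scored as a smoker unless the fourth session fell on day 7. At t2 the same can happen if the session came 3 days or less after quitting. Whatever the session date, 4 of the 7 days at t2 precede app training, and all 7 are also reported at t1 or t3. Comparisons at t2 are therefore diluted, and t2 adds no new calendar days.

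The 4-of-7 figure and the overlaps of 4 and 3 days follow from the stated schedule under the day convention above. The pre-quit counts also depend on d, which the article does not fix, and their effect depends on smoking before the quit day. The 3/7 dilution rests on constant daily rates. The t8 analysis and its power are unaffected. The correction is worth making because following the plan as written gives early results that do not mean what their label says.

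**What to change.** 1. State that t1 is a baseline, and make Primary Efficacy Measure agree with Table 1. Score abstinence at t1 since the quit day.
2. Make between-group comparisons of 7-day PPA from t3 onward.
3. At t2 use only the days since the fourth session. The daily smoking calendar can supply smoking status for those days where it was completed. It records cigarettes, not cravings, so it cannot rebuild the craving count.
4. In the Poisson model use log(days in window) as offset. Do not enter t2 together with a full 7-day t3: even a t2 window cut to 3 days still shares those 3 days with t3. Either drop t2, or let t3 cover only the 4 days since t2.
5. Where t2 cannot be rebuilt, leave it out of the PPA and count comparisons and report it descriptively.

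Recruitment ran to May 2015 and follow-up was under way, so the early assessments may already be collected. The remedy then lies in the analysis, and new question wording helps only participants not yet past t2. The cost is small: t1 and t2 lose the 7-day PPA label, and one early comparison may be dropped. Nothing changes at t8.

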### Eligibility Criteria

All interested participants are screened for eligibility by completing a short battery of questions online. Noneligible participants are advised to contact their doctor or nurse for help. Participants are adults (between the ages of 18 and 65) who have been smokers for at least 1 year and who smoke more than 10 cigarettes per day. (Those who use snus only are excluded.) They should have no other addictions (ie, alcohol, prescription drugs, or illegal drugs) according to the behavioral screening tool NIDA Quick Screen V1.0 [27]. Eligible participants should be addicted to nicotine, with a score of more than 4 out of 10 on the Tobacco Dependence Screener (TDS) [28]. TDS is a 10-item self-report questionnaire, and it generates a continuous dependence score. It demonstrates acceptable reliability in different samples as well as validity because it has a high association with smoking heaviness measures (eg, number of cigarettes smoked per day, carbon monoxide levels) and years of smoking [28-29]. Participants should have a strong motivation to quit and score more than 3 out of 7 on the Motivation to Stop Smoking Scale (MTSS) [30]. The MTSS is a single-item scale assessing an individual’s motivation to quit smoking, combining aspects of desire and intention to quit. Scores range from 1 (I don’t want to stop smoking) to 7 (I really want to stop smoking and intend to in the next month). Participants are also screened for active psychological distress by completing the 12-item General Health Questionnaire [31] and those scoring more than 20 out of 36 are excluded [32,33] because they have lower quit rates [34,35]. Participants are screened for health risks if they increase their physical activity by completing the Physical Activity Readiness Questionnaire [36]. (Those answering yes to any question will be excluded.) Nevertheless, participants who were able to provide permission to exercise from their doctor were accepted to the program. For example, if their blood pressure, heart condition, or bone or joint problem is well controlled with drugs and their doctor says it is safe to exercise.

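### The 7-day abstinence outcome and its saliva cotinine check are applied at session 4 (t1), within a week of the quit day, so verified t1 status partly measures days since quitting

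*Protocol article*

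**What the plan says.** All references are to the protocol article.

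- **Outcome.** Primary Efficacy Measure defines 7-day PPA as "reported abstinence of at least 7 days prior to each scheduled follow-up". It also says: "Self-reports of smoking behavior over the last 7 days are collected from participants at the fourth session", and lists t1 with the later visits.
- **Verification.** The same section says of self-reported PPA that the t1 and t8 "follow-ups are verified by saliva cotinine (with a cutoff value of 10 ng/mL) for stated abstinence using NicAlert saliva-cotinine tests". One cutoff serves both visits. No washout, early-visit rule or consequence of a failed test is stated.
- **Timing of t1.** Smoking Cessation and Relapse Prevention Interventions describes session 4 as one "which is held for the participants within 1 week after their quit day". No minimum interval is given.
- **Population.** Eligibility Criteria admit adults "who have been smokers for at least 1 year and who smoke more than 10 cigarettes per day". The programme before the quit day encourages participants "to gradually decrease smoking and be more physically active", by an amount that is not given.
- **Use of t1.** Statistical Methods makes t8 the primary focus and adds that differences at all follow-up time points will be examined. Primary Efficacy Measure calls t1 a follow-up. Table 1 and Data Collection Procedure start follow-up at t2.

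**The concern.** The t1 visit is one of only two at which abstinence is checked biochemically. The trial randomizes people who have just quit, so a reader will naturally take verified t1 status as confirmation of where they started. If the check at t1 still reads smoking from before the quit day, two equally abstinent participants can receive different results because one was seen on day 2 and the other on day 7. Abstinence at t1 would then look too low, and a description of change from t1 to a later visit could show recoveries that are not behaviour.

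The problem has two parts, and mending one leaves the other. Shortening the self-report window at t1 would not change what the assay reads. Dropping the assay would not change a 7-day window that reaches back past the quit day. Neither part depends on use of nicotine replacement or snus.

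**Working it through.** The protocol gives no figure on this point to reproduce. The check is on timing.

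**Look-back, from the documents alone.** Let d be the days from quit day to session 4, with d at most 7. A 7-day window then reaches 7 − d days before the quit day: 5 days for d = 2, 2 days for d = 5, none for d = 7. Someone who smoked until the quit day and is seen before day 7 cannot truthfully report 7 days of abstinence, however complete the quit.

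**Assay, with assumptions.** Inputs from the document are the 10 ng/mL cutoff, d between 0 and 7, and more than 10 cigarettes per day at entry. Two inputs are assumed because the document gives neither: cotinine at the quit day (C0) of 100 to 400 ng/mL, and an elimination half-life (h) of 12 to 24 hours with first-order decay.

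Days to reach the cutoff = log2(C0/10) × h/24

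| C0 (ng/mL) | h = 12 | h = 16 | h = 20 | h = 24 |
|---|---|---|---|---|
| 100 | 1.66 | 2.21 | 2.77 | 3.32 |
| 200 | 2.16 | 2.88 | 3.60 | 4.32 |
| 300 | 2.45 | 3.27 | 4.09 | 4.91 |
| 400 | 2.66 | 3.55 | 4.43 | 5.32 |

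For example, 200 ng/mL and 16 h: log2(20) × 16/24 = 4.32 × 0.667 = 2.88 days.

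Residual cotinine in a complete quitter = C0 × 2^(−24d/h), in ng/mL:

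| C0, h | day 1 | day 2 | day 3 | day 4 | day 5 | day 6 | day 7 |
|---|---|---|---|---|---|---|---|
| 100, 12 h | 25.0 | 6.2 | 1.6 | 0.4 | 0.1 | 0.0 | 0.0 |
| 200, 16 h | 70.7 | 25.0 | 8.8 | 3.1 | 1.1 | 0.4 | 0.1 |
| 200, 20 h | 87.1 | 37.9 | 16.5 | 7.2 | 3.1 | 1.4 | 0.6 |
| 400, 24 h | 200 | 100 | 50 | 25 | 12.5 | 6.25 | 3.1 |

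Over the assumed grid, a day-1 session always gives a false failure. A day-2 session does so in every case except 100 ng/mL with 12 h. Days 3 to 5 depend on the person. Days 6 and 7 are clear throughout.

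**Share affected, illustration only.** If sessions were spread evenly over days 1 to 7, the share of complete quitters above the cutoff would be the number of failing days divided by 7: 1/7 = 14% (100 ng/mL, 12 h), 2/7 to 3/7 = 29% to 43% (200 ng/mL, 16 to 20 h) and 5/7 = 71% (400 ng/mL, 24 h). If all sessions fell on day 6 or 7, it would be 0%.

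**Sensitivity.** Reduced smoking before the quit day would lower C0: 50 ng/mL with 12 h clears in 1.2 days. In the other direction, 500 ng/mL with 24 h takes 5.6 days, still clear by day 6.

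**The case against.** The strongest reply is that, under the written definition, the assay error hardly arises. A participant seen on days 1 to 5 who smoked until the quit day has no 7-day abstinence to state, so the test has nothing to refute. A participant who can truthfully state it has 7 smoke-free days, and every assumed case is clear by then. This is right about the text. It moves the fault to the look-back without removing it: the genuine quitter seen early still cannot be classified as abstinent at t1.

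Other parts of the reply stand and limit the point:

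- **Consequence of a failed test.** A reader might infer that a positive t1 test reclassifies the participant as a smoker or excludes them. The document says neither. The intention-to-treat group is formed at the quit day/randomization, and participants stay in their assigned groups.
- **Imbalance between arms.** Because session 4 is held separately by group, a reader might infer a spurious difference at t1. Both arms have the same one-week window, and no difference in delay is shown.
- **Role of t1 in the analysis.** No planned model conditions on verified t1 abstinence, and app training only begins at t1, so t1 does not measure the app's effect.
- **Size.** The actual spacing of session 4 is unknown, so the 14% to 71% range is not a forecast and zero is possible.

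The remedy also gives up a biochemical check at one of two visits. That is a real cost, but a check whose result depends on the session date confirms little in the early days.

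**Conclusion.** The point holds for t1 only. As written, the sections on the outcome and on session 4 do not fit together: for sessions in roughly the first 2 to 5 days after quitting, both the 7-day look-back and the cotinine reading capture smoking before the quit day, so verified t1 abstinence partly measures elapsed time.

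The look-back part follows from the document alone and applies to any session before day 7. The assay part rests on the assumed half-life (12 to 24 h) and starting level (100 to 400 ng/mL), under which clearance takes 1.7 to 5.3 days and no false cotinine failure occurs on day 6 or 7.

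It would be tempting to conclude that the trial's main result is at risk. It is not: t8 is 24 weeks after session 4, and cotinine from before the quit day cannot affect it. What is affected is t1 abstinence itself and any description of change from t1 onward. The point deserves correction because the rule cannot classify genuine early-session quitters correctly and the repair is small.

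**What to change.** Reconcile Primary Efficacy Measure with the timing of session 4 in Smoking Cessation and Relapse Prevention Interventions:

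1. Define t1 status as reported abstinence since the quit day.
2. Record the number of days from quit day to session 4 for every participant.
3. Report t1 cotinine descriptively by that interval, and say that it does not override stated abstinence at t1.
4. Keep cotinine verification of 7-day PPA at t8.

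This takes a sentence or two in the outcome definition and no new procedure. Smoking is already self-reported at session 4, the saliva test is already planned, and the quit day is set in session 3. The downside is that t1 status rests on self-report, as at t2 to t7, and the report should say so.
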